## Abstract

**Background:**

Burnout, anxiety, and depression continue to affect physicians, postgraduate medical trainees, and medical students globally and in Canada particularly after the COVID-19 pandemic.

**Objective:**

The primary goal of this project is to design, implement, monitor, and evaluate a daily supportive SMS text messaging program (Wellness4MDs, Global Psychological e-Health Foundation). The program aims to reduce the prevalence and severity of burnout, anxiety, and depression symptoms among physicians, postgraduate medical trainees, and medical students in Canada.

**Methods:**

This longitudinal study represents a multistakeholder, mixed methods, multiyear implementation science project. Project evaluation will be conducted through a quantitative prospective longitudinal approach using a paired sample comparison, a naturalistic cross-sectional controlled design, and satisfaction surveys. Prevalence estimates for psychological problems would be based on baseline data from self-completed validated rating scales. Additional data will be collected at designated time points for paired comparison. Outcome measures will be assessed using standardized rating scales, including the Maslach Burnout Inventory for burnout symptoms, the 9-item Patient Health Questionnaire for depression symptoms, the 7-item Generalized Anxiety Disorder scale for anxiety symptoms, and the World Health Organization–Five Well-Being Index.

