**Conclusions:**

The results from the Wellness4MDs project evaluation will provide key information regarding the effectiveness of daily supportive SMS text messages and links to mental health resources on these mental health parameters in Canadian physicians, postgraduate trainees, and medical students. Information will be useful for informing policy and decision-making concerning psychological interventions for physicians in Canada.

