## Methods

### Study Design

This is a quantitative longitudinal study with data collected from subscribers of the Wellness4MDs program using a web-based survey at the onset of the program and at designated follow-up timepoints. The surveys will include questions related to sociodemographic characteristics, roles, years of training, specialty, work, and clinical information. The Wellness4MDs program will deliver daily supportive and informative SMS text messages with or without embedded web links for mental health support or literacy resources to subscriber cell phones for 6 months. Participation in the surveys would be voluntary, and nonparticipation in any of the surveys will not impact program participation or service delivery. The Wellness4MDs is a national collaborative project that will leverage stakeholder partnerships to disseminate the program to physicians, postgraduate trainees, and medical students. Potential collaborating organizations include the Royal College of Physicians and Surgeons of Canada, faculties of medicine across Canada, provincial medical associations, provincial health authorities, and provincial medical licensing colleges. Initially, promotional material will be provided and give an overview of the Wellness4MDs program and information about how physicians, postgraduate medical trainees, and medical students can subscribe and unsubscribe to the program. Collaborating organizations will be requested to share information about the Wellness4MDs program with physicians, postgraduate medical trainees, and medical students on their databases and social medical handles, including Facebook, LinkedIn, Instagram, and Twitter (rebranded as X). Thus, the Wellness4MDs recruitment plan will mirror the successful recruitment plan of similar programs in Alberta, including the Text4Hope program that was launched in response to COVID-19 in March 2020 [36,37,43] as a collaborative initiative between the University of Alberta, Alberta Health Services, and six health foundations. Text4Hope was the subject of a wide-exposure communications campaign (television, radio, internet, and print media), including the local provincial mental health foundation, Alberta Health Services, and a media release by the provincial chief medical officer [44].

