### Data Collection and Outcome Measures

The project will run for 3 consecutive years. Quantitative data will be collected from subscribers of the Wellness4MDs program using a web-based survey at the onset of the program (baseline), 6 weeks, 3 months (midpoint), and 6 months (end of service) as illustrated in Table 2. The surveys will include demographic questions such as sex and gender, as well as information about their role (physicians, postgraduate trainees, or medical students), their years of training or practice, and their specialty of retaining or practice if they are residents or physicians, in addition to the clinical outcome measures.

Primary outcome measures include changes in the mean scores on the PHQ-9 [51], the GAD-7 [52], the Maslach Burnout Inventory (MBI) [53], and the World Health Organization-Five Well-Being Index (WHO-5) [54] for subscribers from baseline to 6 weeks, 3 months, and 6 months.

The PHQ-9 is a self-administered scale designed to measure likely depression. It is an effective tool for patients and a validated tool for screening of depressive symptoms among the general population [55]. Symptoms experienced by patients during the 2 weeks before answering questionnaires are considered. Scores range from never (0), several days (1), more than half of days (2), to 3 (nearly every day), with every item ranging from 0 to 27 [51,56]. The tool’s reliability and validity have shown good psychometric properties with accepted sensitivity using 10 or above as a cutoff score and high internal consistency (Cronbach α=0.79) [55,57].

The GAD-7 scale is a self-administered valid tool designed to measure likely anxiety [58,59]. The 7 self-reported items are used to assess the severity of generalized anxiety disorder (GAD) symptoms over the past 2 weeks. Ratings are based on a 4-point Likert scale: not at all sure (0), several days (1), over half the days (2), and nearly every day (3). The scores ranged from 0 to 21, with higher scores indicative of more severe symptoms. A sensitivity of 89% and a specificity of 82% for a cutoff score of 10 [59] are considered. The GAD-7 also showed good test-retest reliability (intraclass correlation 0.83), as well as excellent internal consistency (Cronbach α=0.92) [58,60].

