### Statistical Analysis

Quantitative data will be analyzed with descriptive statistics, paired *t* test, and chi-square tests using SPSS Statistics for Windows (Version 25; IBM Corp) [64]. Descriptive data will be presented as numbers and percentages. Paired *t* test will be used to assess the differences in the mean scores of each of the outcome scales for the baseline and the follow-up time points. In addition, the chi-square test will be used to compare the prevalence of burnout, likely GAD and likely MDD, from baseline to the follow-up time points.

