## Discussion

### Principal Findings

The Wellness4MDs project represents an innovative initiative that aligns with 2 main strategic directions, namely, highest quality and proactive and innovative approach. In terms of highest quality, the evidence in favor of the potential effectiveness of the Wellness4MDs program to alleviate stress, burnout, anxiety, and depression among physicians, postgraduate medical trainees, and medical students is derived from meta-analyses of randomized controlled trials and evaluations of related population-level interventions [26,31,32,36-38,40,65-67]. For example, in 2 randomized controlled trials, when CBT-based daily supportive SMS text messages were delivered to patients with MDD either as part of inpatient postdischarge community follow-up care or as part of outpatient clinic care, there was a 50% and 25% greater reduction in mean depression symptoms scores measured on the Beck’s Depression Inventory Scale compared with the control group, respectively [68,69]. Similarly, in an evaluation of the Text4Hope program launched in Alberta during the COVID-19 pandemic, subscribers who had received daily supportive SMS text messages for just 6 weeks had a significantly lower prevalence of moderate to high stress, likely generalized anxiety disorder, likely MDD, suicidal ideation, and disturbed sleep compared with new subscribers during the same time frame [37]. The Wellness4MDs program therefore has the potential to offer physicians an intervention that is of the highest quality with respect to the evidence of effectiveness. The approach to using daily supportive and informative SMS text messages to promote physician wellness would be innovative as it will be the first of its kind globally. In addition to addressing issues of stress, burnout, anxiety, and depression among physicians, residents, and medical students, the embedded web links in some of the messages to be preprogrammed into the Wellness4MDs program are expected to improve the mental health literacy of subscribers and provide information on complimentary mental health resources and approaches that would also be proactive and innovative.

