### Limitations of the Study

This study has a number of limitations. First, the self-reported scales to be used for assessment of the psychological problem, although validated, are not diagnostic. In addition, it is highly probable that the physicians, postgraduate medical trainees, and medical students who are impacted by burnout, stress, or anxiety may be more likely to subscribe to the Wellness4MDs program and so be overrepresented in this study, and thus impact the generalizability of the prevalence estimated for psychological problems. Finally, the duration of the intervention is limited for 6 months; thus, the long-term outcomes after cessation of the service will not be established. These limitations notwithstanding, this study is the first to provide e–mental health support for stress, burnout, anxiety, and depression among physicians, postgraduate medical trainees, and medical students in Canada. This study is a pioneer in assessing if daily supportive SMS text messages delivered through the Wellness4MDs program can reduce the prevalence and severity of stress, burnout, anxiety, and depression, and improve well-being among physicians, postgraduate medical trainees, and medical students. The findings would therefore be of interest to policy makers, especially those working in the health care sector.

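### The abstract promises a controlled comparison that the Methods never define; the stated before-after tests cannot separate a program effect from regression to the mean, yet the conclusions speak of effectiveness.

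*Protocol article*

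**What the plan says.** The Methods paragraph of the abstract lists three components of the quantitative evaluation: "using a paired sample comparison, a naturalistic cross-sectional controlled design, and satisfaction surveys". The first and third return in the main text. The second does not.

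- **Study Design:** one cohort is described, "This is a quantitative longitudinal study with data collected from subscribers of the Wellness4MDs program using a web-based survey at the onset of the program", with follow-up surveys of the same program's subscribers. No comparison group is named.
- **Sample Size Calculation:** 1053, for a standardised change of 0.1 from baseline to 6 months in GAD-7 and PHQ-9, variance 1, two-sided alpha .05, power 90%.
- **Data Collection and Outcome Measures:** the primary outcomes are changes in mean scores "for subscribers from baseline to 6 weeks, 3 months, and 6 months".
- **Statistical Analysis:** paired t tests of the "differences in the mean scores of each of the outcome scales for the baseline and the follow-up time points", and chi-square tests of prevalence, also from baseline to follow-up.
- **Conclusions of the abstract:** the results will give "key information regarding the effectiveness of daily supportive SMS text messages". The Introduction and the limitations section likewise ask whether the messages can reduce symptoms.
- **Limitations of the Study:** affected people "may be more likely to subscribe to the Wellness4MDs program and so be overrepresented in this study". The only stated consequence is for the generalizability of the prevalence estimates.
- **Principal Findings:** an evaluation of the earlier Text4Hope program is cited in which 6-week recipients were "compared with new subscribers during the same time frame". Nothing says that the same comparison will be made here.

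**The concern.** The stated aim is causal: do the messages reduce burnout, anxiety and depression? The one listed element that could give that question a comparator is the controlled design, and it has no groups, time frame, test or sample size. What remains is before-after change in volunteers.

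The protocol itself considers it highly probable that volunteers are more distressed than their peers. If people subscribe during a bad spell, part of the excess fades by itself. Spontaneous recovery and calendar or training-year trends act in the same uncontrolled way. The planned effect of 0.1 SD is small, so a modest drift could produce a significant paired test. That result could then reach policy makers as evidence that the program works.

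**Working it through.** **1. The plan's own figure.** For a paired t test, n = ((1.960 + 1.282)/0.1)² = 1050.7 by the normal approximation. The exact noncentral-t calculation gives 1053 (power 0.9001). The stated 1053 is therefore the size for a before-after contrast with SD of change 1. The same difference between two independent groups would need about 2 × 1050.7 = 2102 per group.

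**2. Regression to the mean.** Let m be the amount, in score SDs, by which subscribers exceed the population mean at enrolment because of a partly transient peak. Let r be the baseline-to-follow-up correlation. The expected score at follow-up with no program effect is r × m above the mean, so the expected fall is (1 − r) × m.

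Inputs: r = 0.83 is the GAD-7 test-retest value in the outcome section. The document gives neither m nor a 6-month correlation, so m = 0.3 to 0.5 and r = 0.6 are assumptions.

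- r = 0.83: 0.17 × 0.3 = 0.051; 0.17 × 0.5 = 0.085.
- r = 0.6: 0.4 × 0.3 = 0.12; 0.4 × 0.5 = 0.20.

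An artefact equal to the whole planned 0.1 needs m = 0.1/(1 − r), which is 0.59 at r = 0.83 and 0.25 at r = 0.6.

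**3. Chance of p<.05 with 1053 pairs and no program effect.** The noncentrality is fall/SD of change × √1053. The document sets a variance of 1 but leaves open whether it belongs to the change or to the score. Both readings are shown. Under the second, the SD of change is √(2(1 − r)), which is 0.583 at r = 0.83 and 0.894 at r = 0.6.

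| r | m | Fall (SD) | SD of change = 1 | Score variance = 1 |
|---|---|---|---|---|
| 0.83 | 0.3 | 0.051 | 38% | 81% |
| 0.83 | 0.5 | 0.085 | 79% | 99.7% |
| 0.6 | 0.3 | 0.12 | 97% | 99% |
| 0.6 | 0.5 | 0.20 | about 100% | about 100% |

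The nominal rate is 5%. If the excess is stable rather than transient, the expected fall is near zero and the rate stays near 5%.

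**4. Would a concurrent comparison cure this?** Take follow-up completers against different, new subscribers at baseline in the same period. New subscribers stand at m and completers at r × m, so with no program effect the groups differ by (1 − r) × m, the same amount as in step 2. With score SD 1 and 2103 per group, a difference of 0.085 gives p<.05 in 79% of studies. With 1053 per group, 0.085 gives 50% and 0.20 gives 99.6%.

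**5. Power of that comparison for a true 0.1 SD.** With 1053 per group it is 63%. The difference detectable at 90% is 3.242 × √(2/1053) = 0.14 SD. About 2100 per group are needed for 0.1 SD.

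**The case against.** Four points on the other side deserve weight.

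- **The article is condensed.** Detail of the controlled design may sit in a fuller protocol, and the program is modelled on Text4Hope, whose evaluation used concurrent new subscribers. A reader might also note that an ordinary chi-square test treats its samples as independent, and that the text does not say the same respondents are compared. This stands to a degree: one cannot say that every listed test is within the same people. But design, outcomes, sizing and tests are all stated, all run from baseline to follow-up, and none supplies a control group.
- **Regression to the mean is not certain.** It needs a transient peak at enrolment. The document does not say whether subscribers' distress is transient or lasting. This stands, so the figures are a conditional range and not an estimate of bias.
- **The hypothesis asks for at least a 20% fall in mean scores.** A fall of 0.085 SD is 20% only if the mean is 0.43 SD (0.085/0.2), and a fall of 0.20 SD only if the mean equals the SD. A reader might infer that any drift of the planned 0.1 SD would automatically count as program benefit. The document does not support that, because its stated target is larger in most settings. However, the analysis section gives no test against the 20% target, only tests of difference.
- **A reader might infer that writing in the promised comparison would make an effect claim safe.** Step 4 shows that it would not. New subscribers are still at their enrolment excess, while completers have already regressed. Adjustment for role, sex or gender, years and specialty does not change that.

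**Conclusion.** The point holds as an inconsistency with inferential consequences. The abstract claims a controlled design that the Methods do not contain, and the conclusions claim effectiveness from uncontrolled change. The document names distress-driven subscription but overlooks what it may do to the before-after contrast.

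The possible artefact, 0.05 to 0.20 SD, is comparable to the planned 0.1. It would raise the false-positive rate from 5% to between 38% and about 100% with SD of change 1, or between 81% and about 100% with score variance 1. These sizes rest on an assumed enrolment excess of 0.3 to 0.5 SD that is transient, and on r of 0.83 (document) or 0.6 (assumed). With stable distress the inflation largely disappears. It is not shown that the bias will occur, only that the stated analysis could not tell it from benefit.

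**What to change.** 1. **Label the paired result for what it is.** Report it as uncontrolled change during the program, not as effectiveness. In the limitations section, name regression to the mean, spontaneous recovery and time trends alongside the point on prevalence.
2. **Reconcile the abstract with the Statistical Analysis section.** Either remove the controlled design from the abstract or define it in the Methods. A workable definition compares follow-up completers with different, new subscribers at baseline in the same quarter. It should be restricted to quarters in which recruitment and follow-up overlap; as Table 1 reads, recruitment ends two quarters before follow-up. Adjust for role, sex or gender, years of training or practice, and specialty, and compare the two groups' own baseline scores.
3. **If it is defined, state its limits.** It addresses calendar trend and shows selection by survey response. It does not remove regression to the mean or survivor bias, so it cannot alone support a causal claim. State also that 1053 per group gives 63% power at 0.1 SD, that 0.14 SD is detectable at 90%, and that 0.1 SD needs about 2100 per group.

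The cost is a weaker conclusion and a little more analysis. The surveys already planned supply the data.

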**Results:**

The project launched in the last quarter of 2023, and program evaluation results will become available within 36 months. The Wellness4MDs program is expected to reduce the prevalence and severity of psychological problems among physicians in Canada and achieve high subscriber satisfaction.

**Conclusions:**

The results from the Wellness4MDs project evaluation will provide key information regarding the effectiveness of daily supportive SMS text messages and links to mental health resources on these mental health parameters in Canadian physicians, postgraduate trainees, and medical students. Information will be useful for informing policy and decision-making concerning psychological interventions for physicians in Canada.

**International Registered Report Identifier (IRRID):**

PRR1-10.2196/44368

## Introduction

Burnout, anxiety, and depression continue to be a problem among physicians globally and in Canada. The recent Canadian Medical Association National Physician Health Survey shows that the well-being of physicians across Canada has significantly decreased [1]. The survey demonstrates that many physicians report poorer mental health than before the COVID-19 pandemic, with 53% of respondents nationally reporting symptoms of burnout, including emotional exhaustion [1]. According to the Medscape National Physician Burnout and Suicide Report, the burnout rate among physicians was reported to be as high as 42% in 2020, compared with 39% in 2013 [2,3]. Similarly, high rates were reported for residents with scores between 41% and 74% across different specialties [4]. Furthermore, 27% of residents stated that they rarely or never had time to lead a satisfying social life; of these, 68% reported having failed relationships for this reason [5,6].

During the COVID-19 pandemic, these figures increased further with about 60% of physicians in Canada reporting that their mental health worsened after the pandemic [7]. Similarly, 35% of a sample of emergency residents demonstrated symptoms of posttraumatic stress disorder acutely during the COVID-19 pandemic crisis [8].

The impact of burnout on the physician workforce is substantial, including a higher likelihood for medical errors, lower quality of care, higher costs, and overall worse outcomes along with reduced patient satisfaction [9-12]. Physicians reporting burnout symptoms work for fewer hours and leave clinical medicine at a higher rate than those not affected, and the resultant decreased productivity may exacerbate physician shortfall [13-15]. In addition, physicians with high levels of distress and burnout are more prone to self-perceived or reportedly commit medical errors [4,16,17]. Furthermore, the risk of depression, stress, alcohol use, and suicidality were increasingly reported among postgraduate trainees who have experienced more working hours, burnout, and less sleep time [4,17,18]. On the other hand, physicians who have high empathy and more positive attitudes tend to demonstrate positive attributes with better clinical outcome profiles in terms of developing better doctor-patient relationships associated with a high patient satisfaction and moral reasoning with clinical competence [19-21]. A recent study investigated the strength and significance of the associations of health workforce with multiple health outcomes and COVID-19 excess deaths across countries, using the latest World Health Organization dataset [22]. The study reported that a higher aggregate density of health human resources, particularly physicians, was significantly associated with healthy life expectancy at birth [22].

Addressing stress and burnout among physicians, postgraduate trainees, and medical students is a priority, given that decreasing rates of medical professionals usually seek psychological help or support. In a study among university hospital physicians in Europe, it was reported that overall, more than 3 in 4 distressed physicians had never sought professional help for depression or burnout [23]. In another study that evaluated the help-seeking behaviors of medical students with burnout and compared their stigma perceptions with those of the general US population and age-matched individuals, it was reported that only a third of respondents with burnout (154/454, 33.9%) sought help for an emotional or mental health problem in the last 12 months [24]. Furthermore, medical students with burnout were more likely than those without burnout to agree or strongly agree with 8 of 10 perceived stigma items [24]. It is well-recognized that the stigma and potential professional reputational damage associated with seeking help for mental health problems often deter many physicians, residents, and medical students from seeking psychological support when they are stressed, burnt out, or dealing with anxiety or depression.

Thus, there was a need for an evidence-based, technology-enabled, cost-effective, and geographic location–independent mental health service to address the psychological problems faced by physicians, postgraduate trainees, and medical students. Previous research examining supportive SMS text messages has demonstrated positive outcomes, in terms of improved clinical symptoms and high user satisfaction [25-27]. In a rigorous evaluation of Text4Mood, an SMS text messaging service launched in Fort McMurray, Alberta to address unmet psychological treatment gaps, it was reported that supportive SMS text messages helped the majority of the subscribers feel more hopeful about managing issues (82%), in charge of managing their depression and anxiety (77%), and connected to a support system (75%). Furthermore, a majority reported that the intervention improved their overall mental well-being (83%) [26]. Similar findings were observed in other contextual studies, such as Text4Baby and quit4baby; the 2 programs that have sought to assist women by providing supportive and informative SMS text messaging during pregnancy [28,29]. Participants in such services indicated that receiving these messages gave them a sense of reassurance and made mothers feel supported, particularly in disadvantaged communities [30]. Similarly, texting services, such as Text4Support, have effectively reduced the risk of harm to self and other harm symptoms after 6 months of intervention in a randomized controlled trial [31] and reduced distress, anxiety, and depression symptoms in clinical samples [32]. In addition, the Text4PTSI program has achieved fidelity and significantly reduced psychological distress among public safety personnel post intervention [33,34]. Furthermore, during the COVID-19 pandemic, people needed to feel connected to a health support system. Text4Hope service was provided to support the mental health of the general public in Alberta; the service reported a significant reduction in stress, anxiety, depression symptoms, and suicidal ideation during the pandemic [35-38]. Another related service, the Text4Hope-Addiction program was introduced to people living with substance use disorders [39]. The service reported significant improvement in standardized measures for craving, anxiety, and depression in subscribers. SMS text message–based population-level messaging programs have reported user satisfaction rates of well over 80%, and most subscribers have reported feeling connected to support systems and improving their ability to manage anxiety, depression, and general life issues, suggesting an improvement in mental health literacy [26,27,40-42].

In this study, we propose the Wellness4MDs (Global Psychological e-Health Foundation) initiative, a text-based proposed program that will deliver daily supportive and informative SMS text messages with or without embedded web links for mental health support or literacy resources to the physicians in Canada for 6 months. The Wellness4MDs program SMS text messages are based on cognitive behavioral therapy (CBT) principles and developed by psychiatrists, mental health therapists, clinical psychologists, and users of mental health services. Wellness4MDs program may help provide a first-line intervention that addresses the help-seeking barrier of stigma that fits with the busy lifestyle of physicians, postgraduate trainees, and medical students.

The goal of this project is to support the mental health of physicians, postgraduate trainees, and medical students in Canada using a daily supportive SMS text message. We aim, first, to evaluate the prevalence and correlates of burnout and probable mental health symptoms and, second, to determine if daily supportive SMS text messages can help reduce the prevalence and severity of these symptoms and improve well-being among subscribers in Canada. We will also assess the experience and satisfaction of the Wellness4MDs program subscribers with the daily supportive SMS text messaging program.

